### Study design

A cross-over design was chosen for this study as it improves statistical power by making each participant a baseline for themselves. It is also driven by the need to achieve sufficient buy-in from the participants and their coaches—the groups known for their dislike for passive control designs where participants in control conditions can miss out on the potentially beneficial intervention.

In our cross-over design participants will be randomly assigned to either a “training-first” or “waiting first” group. All participants will complete baseline assessment using methods (described in “Outcome measures”) at the start of Week1 (Time 1), then repeat it at the start of Week 4 (Time 2) and at the completion of Week 6 (Time 3). A single blind strategy will be utilized, with researchers administering pre- and post-assessments having no access to the information on which group the participants belong to (training-first or waiting-first).

Following Time 1 assessment, the “training-first” group will commence the three-week training program described in Section 3.3 above, spending 30 min a day practicing the drills delivered through the Cognitive Gym app. The “waiting first” group will have no engagement with the Cognitive Gym app for the first 3 weeks but will have access to the companion website for the designated 30 min daily. They will commence their three-week training with the app immediately after Time 2 assessment. Access to the app will cease for the “training-first” group after Time 2. As a result, each participant will go through 3 weeks of Cognitive Gym app-supported training and 3 weeks waiting, with half of them randomly assigned to training first and then waiting, and the other half—to a reverse order. Coach ratings of athlete progress will be examined in the evaluation, so their consent to participate will also be sought.

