### Cognitive gym training program: Practice drills

The initial version of the app was designed to satisfy a “proof of concept” requirement for the project. For this purpose, the selected drills were combined into a single intervention to form a Cognitive Gym. The intervention employs a blended delivery methodology, combining face-to-face pre-brief with a three-week program *via* a web application that is designed to help participants exercise their primary cognitive capacities and performance-focused cognitive skills. The web application contains educational videos, guided cognitive workouts, breathing sessions, user engagement tools, completion trackers, leaderboards, and a social feed. The Cognitive Gym also uses gamification techniques to consolidate behavior change.

The current prototype (see Supplementary material S2, panels A,B) contains a recommended sequence of 2 h of instructor-led learning followed by one-and-a-half to 3 weeks of 30-min daily practice. This core sequence includes:

Program “brief in” introducing the intervention as “cognitive fitness training” similar to conditioning and skill training work. Included in the briefing is an education section on developing a “high performance mindset” and on developing understanding and control of attentional flexibility. Participants will be encouraged to apply their knowledge of those areas to their cognitive fitness work. This two-hour instructor-led instruction was accomplished by preparing a set of eight introductory videos promoting the use of the app to achieve a high-performance mindset. The additional Web resources described earlier are also available to the trainee.Daily 30 min practice involves ten sequential drills, guided by a mobile device-based app with built in engagement functionality to encourage participants’ continued involvement. The ten drills are described below.

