#### CogMission platform

The CogMission online testing platform (Wells et al., 2021; Kucina et al., 2022) delivers a testing protocol based on a gamified dynamic scenario containing trials made up of the following three tasks, all requiring a binary response by pressing either the Left (z) or Right (/) key on the keyboard:

Working memory basic task. Participants are asked to remember which of three doors was highlighted two trials ago and what symbol (0/×/+) is present on the door, then use that information to decide if the door highlighted on the current trial matches.Stop-signal task. This is a classical task used to measure response inhibition (Matzke et al., 2018). An arrow appears on the highlighted door and the participant notes which direction it points. If a red outline appears around the door after the arrow appears (25% of trials) the participant must withhold their response. The stop-signal delay (from the onset of the arrow to the red frame over the door) is adjusted over trials to ensure that stopping is successful on approximately 50% of trials.Selective attention task. The task measures the ability to control interference from irrelevant spatial and verbal information using Stroop (MacLeod, 1991) and Simon tasks (Hommel, 2011), and information from irrelevant spatial locations using a Flanker task (Eriksen, 1995). The door opens, the room behind is shown, a cue at the top of the screen indicates the side where opposition is hiding, and the participant must press the corresponding button. Cues can be the direction of a central arrow (surrounded by flanking arrows: left = <<<<< or > > <>>, right = >>>> > or > > <>>) or the color (e.g., left = blue, right = orange) of a rectangle or word (“BLUE” or “ORANGE”). Two such decisions are made in sequence on each trial, sometimes with the same type of cue and sometimes with different cues. This allows measurement of cognitive flexibility in terms of updating goals using a task switching paradigm (Monsell, 2003). That is, on each trial participants perform two conflict task trials in a row. When the two tasks are the same, the second trial does not require updating the goals established by the first (a “repeat” trial). If the two tasks differ the second trial requires updating of goals (a “switch” trial). Slower response times on switch trials relative to repeat trials indicate reduced flexibility.

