#### Athlete self-ratings

Cognitive Fitness self-assessment, a set of 20 self-rating scales assessing the individual’s perception of their typical cognitive performance over the preceding 3-week period. Details are in Supplementary material S1.

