#### Coach ratings

Coach assessment of “far transfer”: to ascertain the extent of training gains transfer to the sporting contexts, athletes will be rated by their coaches. Coach ratings assess the athlete’s attributes such as composure in competition (e.g., 1 = cool, 2 = calm, 3 = worried, 4 = flustered) and adaptability (e.g., 1 = rigid; 2 = gets stuck; 3 = flexible; and 4 = fully adaptive). More details are in Supplementary material S1.

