### Planned analyses

It is expected that, with practice, participants will improve their performance scores on the respective drills. These changes will be monitored and evaluated throughout the intervention. A single blind strategy will be utilized, with researchers administering pre- and post-assessments having no access to the information on which crossover group the participants belong to (training-first or waiting-first).

Improved scores on the drills, however, is no guarantee that participants have learned skills that transfer to similar cognitive tasks (i.e., near transfer), such as the working memory, response inhibition, and cognitive flexibility tasks included in the CogMission battery. Near transfer effects will be evaluated by estimating training gains defined as differences between each CogMission measure at baseline and at the end of the Cognitive Gym training.

Repeated measures ANOVA and mixed linear modelling will be used to estimate effect sizes. Effect size of *d =* 0.4 on training-induced change is considered meaningful and practically important, based on a meta-analysis of randomized controlled trials examining the effects of similar programs on stress (Dhir et al., 2021). This effect size corresponds to *f =* 0.25 for ANOVA power calculations. To reliably detect effects of this size, with two groups and three repeat measurements in our design, G*Power calculations return a minimal sample size of 28 participants (Faul et al., 2009). Allowing for sample attrition and the uncertainty associated with extrapolating power calculations for mixed linear modelling, this study will aim to recruit 60 participants.

Far transfer effects will be evaluated through the coach and athlete ratings. Despite some well-known limitations of self-reports, they have advantages such as easy interpretability, information richness, and practicality (Paulhus and Vazire, 2009). Similar ANOVA and mixed linear modelling will be applied to assess training gains on these measures. Evidence of both near and far transfer effects will address the frequently-voiced objections that gamification techniques lead to improved performance in the games themselves but not in the broader skills they are meant to develop.

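### The stated single blind covers only the researchers who administer assessments; far transfer is judged by athletes, who know their allocation, and by coaches, for whom no masking is stated

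*Protocol article*

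**What the plan says.** The Study design section defines the blind by naming whom it covers: a single-blind strategy "with researchers administering pre- and post-assessments having no access to the information on which group the participants belong to". Planned analyses repeats it with the same scope. Neither place mentions coaches or athletes.

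Outcome measures lists three sources of efficacy data:

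- **CogMission**, which "delivers a testing protocol based on a gamified dynamic scenario" online and is answered by key press.
- **Athlete self-ratings**, 20 scales on the athlete's "perception of their typical cognitive performance over the preceding 3-week period".
- **Coach ratings**, for which "athletes will be rated by their coaches" on attributes such as composure and adaptability.

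Planned analyses then assigns the second and third to far transfer: "Far transfer effects will be evaluated through the coach and athlete ratings".

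In Weeks 1 to 3 the training-first group uses the app, and the waiting-first group has the companion website only. The roles reverse after Time 2. Study design also gives acceptance by athletes and coaches as a reason for the cross-over, because both groups dislike designs in which controls may miss a possible benefit.

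**The concern.** Blinding matters most where an outcome depends on judgement. Here both judgement-based outcomes come from people whom the stated blind does not cover. The administrators, whom it does cover, are given no rating task in the article.

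The stake is the far-transfer conclusion. Outcome measures presents far transfer as central, and Planned analyses expects evidence of near and far transfer to answer the criticism that gamified training improves only the games. If raters know who has trained and expect it to help, a rating difference does not answer that criticism.

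The cross-over does not remove the problem. A rater who knows the sequence knows which three weeks were training for each athlete, so expectation can favour the training period in both sequences.

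**Working it through.** **Step 1. Who produces each outcome, and does the stated blind cover that person?**

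| Outcome (Outcome measures) | Used for | Who generates the value | Covered by the stated blind? | Knows allocation? |
|---|---|---|---|---|
| CogMission | Near transfer | Athlete's key presses, online | Administrator only | Athlete: yes |
| Self-ratings, 20 scales | Far transfer | Athlete | No | Yes, unavoidably (app or no app) |
| Coach ratings | Far transfer | Athlete's own coach | No | Not stated; nothing prevents it |

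Both far-transfer rows read "No" in the fourth column. That is the finding, and it needs no arithmetic. Two features of the article bear on the coach row. Participants says that all members of selected squads aged 18 to 30 are invited, so one coach may well rate athletes from both sequences. Study design says that coaches' consent is sought, so they know that the study is running.

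**Step 2. The plan's own figure.** The article gives no number on blinding. Its one sample-size figure is a minimum of 28 for f = 0.25, two groups and three measurements. I assumed alpha 0.05, power 0.80, correlation 0.5 and sphericity, none of which is stated. The within-between interaction test then has noncentrality f² × N × m / (1 − ρ) = 0.0625 × 28 × 3 / 0.5 = 10.5 on 2 and 52 degrees of freedom, and power 0.812. The figure of 28 is reproduced. The blinding point does not depend on it.

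**Step 3. Illustration of what an expectation shift would do.**

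Inputs:
- n = 30 per group, half of the recruitment target of 60, with full retention assumed.
- No true effect; two-sided alpha 0.05 (assumed).
- Correlation between Time 1 and Time 2 ratings ρ = 0.5 (assumed).
- Shift b, in SD units, between groups at Time 2 from knowing allocation (assumed).

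Formula: noncentrality δ = b / √(2v/n). The rate is the probability that a noncentral t exceeds the upper 2.5% critical value.

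- Baseline-adjusted: v = 1 − ρ² = 0.75, so √(2 × 0.75 / 30) = 0.2236.
- Change score: v = 2(1 − ρ) = 1, so √(2 × 1 / 30) = 0.2582.

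| Assumed shift b (SD) | δ, baseline-adjusted | False favourable result, baseline-adjusted | False favourable result, change score |
|---|---|---|---|
| 0 | 0 | 2.5% | 2.5% |
| 0.2 | 0.894 | 14% | 12% |
| 0.3 | 1.342 | 26% | 21% |
| 0.4 | 1.789 | 42% | 33% |
| 0.5 | 2.236 | 59% | 48% |

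The 0.4 row is of interest because Planned analyses calls d = 0.4 meaningful: a rating shift of that size would look like the effect sought. The table models a Time 2 comparison. The plan is for repeated-measures ANOVA and mixed models over three assessments, so the exact rates would differ.

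**The case against.** The strongest reply is that the article makes no false claim. It says precisely who is blinded, and never says that the blind protects far transfer. That stands: a reader might infer from the single-blind label that the ratings are protected, or accuse the article of saying so, but the text supports neither.

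Other stronger readings also go beyond the document:

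- *Coaches know the allocation.* Not stated. Their masking status is left open, and the supplement with the rating details, which is not shown, may address it.
- *Coaches see the app's displays.* The app includes "completion trackers, leaderboards, and a social feed", but these are described as features for participants, and nothing gives coaches access. Daily contact between coach and athlete is not stated either.
- *The administrators' blind is worthless because they score nothing.* The absence of a scoring role is an inference from the outcome descriptions. Masking administrators can still keep instruction and encouragement even.

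There are also mitigations. The waiting group has the website for the same 30 minutes a day, which narrows the difference in attention. CogMission provides an objective measure to read beside the ratings. The article concedes that self-reports have limitations. This is a proof-of-concept study, and athletes cannot be masked in any comparison of app with no app.

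All of this lowers the tone of the point but does not remove it. Website access does not hide allocation, CogMission addresses near transfer, and the remark on self-reports does not deal with coach expectation. Silence on coaches matters more here than an ordinary omission, because the article states the blind's scope twice and coaches are in neither statement.

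**Conclusion.** The point holds in a limited form. As described, the blind covers the administrators only. Self-ratings are certainly unblinded, and coach ratings have no stated protection, so a favourable far-transfer result could reflect expectation. It would be too strong to say that such a result must be bias or that coaches will know the groups.

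The illustrative rates of 14%, 26% and 59% for shifts of 0.2, 0.3 and 0.5 SD rest wholly on assumed shifts, together with the assumed correlation, full retention and a Time 2 analysis. They show how sensitive the conclusion would be; they are not estimates for this trial. The qualitative finding needs none of these assumptions. It concerns far transfer and does not undermine the CogMission results. The change is worth making because it costs little and leaves the design intact.

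**What to change.** In Study design and Planned analyses:

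1. State who is masked and who is not: administrators masked, athletes not masked, and coaches masked to sequence as raters.
2. Do not release allocation to coaches until after the Time 3 ratings. If they would otherwise have access to any app display that reveals it, withhold that access for the same time.
3. Ask athletes not to tell their coach which group they are in.
4. At Time 2, have each coach record a guess of each athlete's group, and report the guesses beside the coach-rating results.
5. Base the far-transfer conclusion mainly on coach ratings, and describe self-ratings as unblinded and supportive.
6. If coaches cannot be masked, state that both far-transfer ratings are unblinded and limit the far-transfer conclusion accordingly.

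**Cost:** one instruction to athletes, one extra question to coaches, possibly an access setting, and a few sentences of text. No extra staff or participants are needed. **Downside:** masking may be imperfect, since coaches may notice or be told who is training, and they learn the allocation later than they otherwise might. The recorded guesses would help to show how far the masking held.

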## Prototype intervention

Table 2 summarizes the range of cognitive constructs and training objectives that could be addressed by a mobile app. When one considers that it takes sustained practice to acquire mastery of any of the elements in the last column of Table 2, it becomes evident that the range of training targets is far too large for any app. Our review of sports-related apps currently on the market suggests that most of them are modest in their offerings. They provide feedback on a narrow range of biomarkers and/or they concentrate on a limited range of skills (e.g., controlled breathing). Faced with this same dilemma for the initial version of our app, we decided to develop web-based resources that users could consult to gain a better understanding of psychological skills underpinning high performance and how they can be trained using the app. These web-based resources are more than an optional add-on, they form an essential component of the intervention, and will be described next.

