The key sub-pages referring to principles embraced by elite performers contain the pre-briefing video material that participants are required to interact with before commencing their training program *via* the app.

Page 6 is headed “Definitions,” and contains a glossary of terms used both in the Website and the app. It is designed to facilitate participants progressing through their training program with an unambiguous explanation of key concepts.

Page 7 is headed “References,” and contains a systematic collection of links to additional materials and sites relating to the concepts contained in the website and the training program contained in the App.

Page 8 is headed “Stories” and contains case study examples of athletes requiring or using the skills developed in the training program. These case studies inform participants’ understanding of the relevance of the drills that comprise the training program.

The last page is headed “More.” It contains links to other resources, such as papers, infographics or talks on topics of interest to those seeking to improve performance or overall wellbeing. Examples include special breathing techniques, heart rate variability, performance debriefing, and how to better cope with the lifestyle demands of performing in high expectation environments.

Although the website adds some further resources for those looking for ways to improve wellbeing and performance, at its core are the pages supporting the app, which we will now describe.

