
The drills are the building blocks of the Cognitive Gym. They will be administered either alone or in combination (e.g., imagery drills preceded by breathing drills). Combinations comprise as many as five different drills arranged as loops, sequences, spirals, or other sequences. Each drill involves systematic and disciplined execution of underpinning cognitive skills, such as concentration, endurance, and attentional flexibility. The core instruction is delivered *via* the smartphone mobile app (see Supplementary material S2, panels A and B) and backed by the companion website described above, which offers extensive background information and additional practice options.

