## Evaluating the cognitive gym prototype: Methods

It is important to evaluate the prototype app in the context of a well-defined Cognitive Gym training package catering for a well-defined user group. The current proof-of-concept study will evaluate the app-supported Cognitive Gym training package in a sample of competitive athletes. The evaluation will assess training gains and participants’ engagement with the app. More details are given below.

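### The waiting-first group receives the companion website, which the plan counts as part of the intervention, so the randomised contrast measures the app's added effect and not the efficacy of the package

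*Protocol article*

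**What the plan says.** All references are to the protocol article.

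- **What the control receives.** Under *Study design*, the website is open to waiting-first participants, who "will have access to the companion website for the designated 30 min daily". Only the app is withheld from them: they "will have no engagement with the Cognitive Gym app for the first 3 weeks". The training group's drill practice is also set at 30 minutes a day. The control period is labelled waiting: "each participant will go through 3 weeks of Cognitive Gym app-supported training and 3 weeks waiting".
- **Status of the website.** *Prototype intervention* says that the web resources go beyond an optional extra and that "they form an essential component of the intervention".
- **What the website holds.** In *Building the app: Web materials*, the key sub-pages of the briefing section "contain the pre-briefing video material that participants are required to interact with before commencing their training program". The site also carries imagery, relaxation and breathing material. *Cognitive gym training program: Practice drills* describes the site as one "which offers extensive background information and additional practice options".
- **The briefing is part of the core programme.** The same section puts a two-hour brief-in at the head of the core sequence and says how it is delivered: "This two-hour instructor-led instruction was accomplished by preparing a set of eight introductory videos".
- **What is to be evaluated.** *Evaluating the cognitive gym prototype: Methods* says that the study "will evaluate the app-supported Cognitive Gym training package in a sample of competitive athletes". *Outcome measures* speaks of the efficacy of the Cognitive Gym protocol. *Requirements for an effective app* expects far transfer from the app together with its supporting materials.

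**The concern.** The plan withholds one component of its package (the app) from the control and supplies another (the website), yet it describes the control as waiting and the target as the package. A reader of the results would naturally take the between-group difference as the effect of the Cognitive Gym programme against doing nothing. As written, it is the effect of adding the app to material that both groups can use.

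This affects attribution. *Concluding comments* says that the evidence will guide further development of the training package, the app and the supporting materials, and it names reliance on the web-based tools as a major difference from other platforms. If the website contributes to cognitive fitness, as the plan expects, that contribution cancels out of the randomised comparison. A null finding could then count against a programme that works.

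**Working it through.** No figure in the plan needs recomputing for this point. The check is to set out what each group receives and what each comparison can therefore estimate.

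**Step 1. Conditions by period, from *Study design*.**

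| Group | Time 1 to Time 2 (weeks 1–3) | Time 2 to Time 3 (weeks 4–6) |
|---|---|---|
| Training-first | App, with website and briefing | App access ends; website access not stated |
| Waiting-first | Website, 30 min a day, no app | App, with website and briefing |

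No section restricts the waiting group to particular pages. The website time open to that group, if used on every day of three weeks, is 21 × 30 min = 630 min = 10.5 hours. The briefing takes 2 hours. This is time available; actual use is unknown.

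**Step 2. What the Time 1 to Time 2 contrast estimates.** Let P be the effect of the whole package (app, briefing, website) relative to nothing, and W the effect of website access alone relative to nothing. Then

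contrast = P − W.

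The package effect is P. The two agree only if W = 0, and the plan's description of the website as essential argues against assuming that.

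**Step 3. How each result reads.**

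- *Positive contrast.* If W ≥ 0, then P ≥ P − W > 0. The app adds something, and the estimate is a conservative one for the package.
- *Null contrast.* P − W = 0 means P = W. That holds when both are zero (nothing works) and equally when both are positive (the website delivers the benefit and the drills add nothing). The trial data do not separate the two.

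**Step 4. The second period.** *Study design* ends app access for the training-first group after Time 2 but does not mention the website. If that group keeps the website, the second non-app period matches the first on access, and the contrast, carry-over aside, is again P − W. If it loses the website, the contrast is P, again leaving carry-over aside. Averaging the two periods with equal weight would then give ((P − W) + P)/2 = P − W/2, which is neither quantity. The article does not say which case applies.

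**Step 5. Does the within-person gain rescue the package effect?** *Planned analyses* defines near-transfer gain as the difference between baseline and the end of training. Taken within a person, this has no control for practice on a repeated test battery. If baseline means Time 1, the waiting-first group's gain also spans three weeks of website access. It does not supply P.

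**The case against.** The strongest defence is that the comparator is deliberate and good. *Study design* says that athletes and coaches dislike passive controls and that buy-in drove the choice. A control matched for time also helps with attention and expectancy, which matters because only the assessors are described as blinded and the outcomes include self-ratings. Parts of the article treat the drills as the tested element: they are called the building blocks of the Cognitive Gym, and the website its companion. On that reading the contrast fits the aim and only the wording is loose.

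Most of this stands. It justifies the comparator, but not the label of waiting or a package-level conclusion from it, and the package wording in the Methods and *Outcome measures* sections remains.

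It is also fair to say that no sentence tells the waiting group to watch the briefing videos in weeks 1 to 3; they are tied to the start of app training. But no sentence keeps them back either. Details of access are often left to a full protocol. The conflict between calling the website essential and calling the control waiting is nevertheless in the printed text.

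Three stronger readings are tempting and are not supported:

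- *That the trial cannot show anything about the programme.* Step 3 shows that a positive result does bear on it if the website does no harm.
- *That the planning effect of d = 0.4 is too large for this contrast.* *Planned analyses* takes it from a meta-analysis of randomised trials of similar programmes on stress, without giving their comparators, and presents it as a meaningful difference.
- *That power falls by a stated amount.* This would need the share of the effect that the website delivers, which no document gives.

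**Conclusion.** The point holds as one about the estimand and its labelling. The randomised Time 1 to Time 2 contrast is a valid test of what the app adds to the website. It does not estimate the efficacy of the package or protocol that the Methods and *Outcome measures* sections name. The shortfall is W, the website's own effect; its size is unknown and no number should be attached to it. The consequence is asymmetric: a positive result is conservative for the package provided that the website does no harm, while a null result is uninterpretable for the package.

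The conclusion assumes that the waiting group can use the site as described, with no restriction on pages. If the full protocol limits that group to pages outside the intervention, the concern shrinks accordingly.

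A reader might infer that the website should be closed to the waiting group until Time 2. The documents do not require that: it would give up the time-matched control and cut against the stated buy-in reason, so it is a design trade-off and not a correction.

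**What to change.** Reconcile *Prototype intervention*, *Evaluating the cognitive gym prototype: Methods*, *Study design* and *Outcome measures* on what is compared with what:

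1. In *Study design*, replace the waiting label with a time-matched website (active) control, and say which parts of the site that group may use.
2. Define the estimand as app plus website versus website alone.
3. Limit efficacy conclusions to the app's added effect, and say that a null result will not be read as evidence that the package is ineffective.
4. State whether the training-first group keeps website access in weeks 4 to 6, so that the two non-app periods are the same condition or are openly treated as different.

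Items 1 to 3 cost only wording. Item 4 is one decision about access, plus a log-in setting if current practice differs between the groups. Sample size, outcomes and visit schedule do not change.

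### The two waiting periods are described differently, yet the design says both groups receive the same training and waiting conditions in reverse order

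*Protocol article*

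**What the plan says.** Study design randomises athletes to training-first or waiting-first and assesses everyone at the start of Week 1 (Time 1), the start of Week 4 (Time 2) and the end of Week 6 (Time 3). The two waits are described as follows.

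- **Waiting-first, Weeks 1-3:** no app, "but will have access to the companion website for the designated 30 min daily".
- **Training-first, Weeks 4-6:** "Access to the app will cease for the “training-first” group after Time 2". Nothing else is said about these three weeks.

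The section then concludes that "each participant will go through 3 weeks of Cognitive Gym app-supported training and 3 weeks waiting". It presents the two sequences as the same pair of conditions, taken by one randomised group in one order and by the second group in the opposite order.

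The article does not treat the website as inert. Under Prototype intervention it says of the web resources that "they form an essential component of the intervention". Under Building the app: Web materials, the key sub-pages "contain the pre-briefing video material that participants are required to interact with before commencing their training program". The practice-drills section adds that the site holds further practice options.

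Planned analyses names repeated-measures ANOVA and mixed linear models, and bases the sample size on two groups with three measurements.

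**The concern.** A two-period cross-over gains its strength from both sequences receiving the same two conditions. The second period can then be set against the first, and each athlete's own waiting period can serve as the control. Here one wait carries a designated daily website slot. The other, as written, is simply the end of app access. The statement that the second group receives the reverse order does not follow from the conditions given just before it.

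At stake is what the second period can show. If website time has any effect of its own, the second-period contrast is not the counterpart of the first. A model using all three time points would then average two different comparisons under one label. Self-ratings and coach ratings could plausibly respond to a structured daily slot as well as to the drills.

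**Working it through.** **The plan's own figure.** With f = 0.25, two groups and three measurements, and assuming alpha 0.05, power 0.80, correlation 0.5 and sphericity (none of these is stated), the noncentrality is f²·N·m/(1−ρ) = 0.0625 × 28 × 3 / 0.5 = 10.5 on 2 and 52 degrees of freedom. Power is 0.812, so the stated minimum of 28 is reproduced. It does not settle the present point, which concerns what is being compared.

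**What each group has, as written**

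| | Weeks 1-3 | Weeks 4-6 |
|---|---|---|
| Training-first | App, 30 min a day | App ceases; nothing designated |
| Waiting-first | No app; website access, designated 30 min daily | App, 30 min a day |

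If the slot applies on all 21 days, designated access during the wait is 21 × 0.5 h = 10.5 h for waiting-first, against none designated for training-first. This is access offered, not time spent.

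**What the contrasts estimate.** Let T be the training gain, w the gain during the website wait, n the gain during the undesignated wait, and p1 and p2 the period effects common to both groups. Let c be carry-over of training into the later wait, and c′ carry-over of the website wait into later training. The changes are:

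- training-first: p1 + T, then p2 + n + c
- waiting-first: p1 + w, then p2 + T + c′

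Between groups:

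- Period 1 (training-first minus waiting-first): T − w
- Period 2 (waiting-first minus training-first): T − n + c′ − c
- Gap (Period 2 minus Period 1): (w − n) + (c′ − c)

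Within person, training minus waiting:

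- training-first: T − n + (p1 − p2) − c
- waiting-first: T − w + (p2 − p1) + c′
- Gap (training-first minus waiting-first): (w − n) + 2(p1 − p2) − c − c′

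The comparator difference w − n always appears summed with carry-over and, within person, with period effects too. Two sequences with three assessments cannot separate these terms. The Period 1 between-group contrast contains neither n nor carry-over.

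**Size, for illustration.** Take T = 0.4 (the plan's meaningful effect), n = 0 and no carry-over. The documents give no w, so 0 to 0.2 is an assumed range.

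| w | Period 1: 0.4 − w | Period 2: 0.4 | Average: 0.4 − w/2 | Gap w as share of 0.4 |
|---|---|---|---|---|
| 0 | 0.40 | 0.40 | 0.40 | 0% |
| 0.1 | 0.30 | 0.40 | 0.35 | 25% |
| 0.2 | 0.20 | 0.40 | 0.30 | 50% |

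On the plan's own scaling (f = 0.25/0.4 × d) and the assumptions above, the minimum N for the average contrast is 28, 36 and 48. All are below the recruitment target of 60, before attrition. In this range the main cost is to interpretation rather than power.

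**The case against.** The strongest reply is that this is silence in a condensed article. The text does not say that website access ends for training-first after Time 2. The reverse-order sentence could be read as extending the same wait to both groups, and the full protocol may spell this out. Part of this stands: a reader might infer that training-first loses the website, and the article does not support that. What it supports is that no slot or activity is designated. It is still more than missing detail, because the article describes both waits, describes them differently, and then states a symmetry that does not follow.

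Second, waiting-first is given access and is not said to have to use it, whereas the training group is described as spending its 30 minutes practising. This stands. It would be wrong to infer 10.5 h of activity received, or a fully time-matched control.

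Third, w is unsupported by the documents and may be zero. This stands; the percentages only restate the assumed range. If training-first athletes keep using the site, n may also be above zero and the gap smaller.

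Fourth, near-transfer gain is defined from baseline to the end of training, and nowhere does the article say that both waits are pooled as one condition. This stands in part. However, the cross-over is justified by each athlete serving as their own baseline, and the sample size rests on two groups with three measurements, so training-first Time 3 is expected to carry information.

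Finally, equal website slots would not make Time 3 the mirror of Time 2. Training effects may persist, and training-first athletes will already have used the site. This is correct and limits what the fix can achieve.

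**Conclusion.** The point holds in a limited form. As written, the two waiting periods are different comparators, and the claim that both groups receive the same conditions in reverse order does not follow from the conditions described. The second-period contrast is with no designated activity, while the first is with designated website access. Their difference is mixed with sequence, period and carry-over in a three-time-point model.

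Its size cannot be fixed from the documents. Over an assumed website effect of 0 to 0.2 in d units, with no gain in the undesignated wait and no carry-over, the two period contrasts differ by 0 to 0.2, or 0-50% of d = 0.4.

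A reader might go further and conclude that the whole efficacy comparison is compromised. The documents do not support that. The randomised Time 1 to Time 2 contrast compares the app with designated website access and is untouched by what training-first does afterwards. Whether the website is a suitable comparator there is a separate question. The damage is confined to the second period and to any within-person or pooled analysis that uses it.

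**What to change.** Amend Study design in one of two ways, before any training-first athlete reaches Week 4, since exposure cannot be equalised afterwards.

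1. Define one waiting condition and apply it to both groups: the same website access and the same daily slot in Weeks 1-3 for waiting-first and in Weeks 4-6 for training-first. This removes an avoidable asymmetry but not carry-over, and the text should say so. The cost is a sentence in the protocol, use of a website that already exists, and a light daily slot for training-first athletes in Weeks 4-6.
2. Otherwise, delete the reverse-order statement, base the between-group efficacy conclusion on the Time 1 to Time 2 contrast, and state that training-first Time 3 is not a waiting control but is read as follow-up after training. The cost is the loss of the second-period control information.

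Under either option, state what website access and daily activity each group has while waiting.
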